### 2.13. Compliance with Trial Treatment

The follow-up visits are important for the successful completion of this trial. Compliance with clinical visits at designated intervals will be ensured by either a telephonic reminder call or a text message to participants. The appointments may be rescheduled two days earlier or later if the participant wishes to do so or inadvertently misses an appointment. Non-compliance will be recorded if the participant fails to report for two rescheduled appointments, and the participant will be withdrawn from the trial. However, if the subject completes two revisits and thereafter becomes non-compliant, the person-time of participation in the clinical trial will be included in the analysis.

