### 2.8. Primary Outcomes

#### 2.8.1. Assessment of Survival of the Restoration 

The follow-up will be conducted on the 7th and 30th days, and the end of the 6th month to evaluate the survival of the restoration (Table 1).

Each restoration will be assessed according to codes and criteria used in ART studies as proposed by Jo E Frencken [13]. Cavities treated with SDF and ART will be considered arrested caries lesions when the tooth surfaces with active caries at baseline visit change into surfaces with arrested caries beneath an intact restoration. The restored tooth is asymptomatic and clinically functional.

In the SDF and ART or ART-treated tooth, if caries progress beyond the dentine, it will be considered not arrested. In such conditions, the patients will be advised to follow standard treatment protocols. During the follow-up period, if the restored tooth is extracted due to infection, trauma, or fracture, the concerned tooth will not be included in the study.

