Once an individual is enrolled in the trial, an appropriate effort will be taken to follow the study participant for the entire study period of six months. Each patient will have the right to withdraw from the trial at any time. If it is due to an adverse event, review visits will be arranged by the PI until the adverse event has been resolved. There will be no restrictions in case the trial participant requires any dental treatments other than that of the concerned tooth.

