## 4. Statistical Methods

The observed data will be coded, tabulated, and analyzed using Statistical Package for Social Sciences (version 20). We will assess the outcomes at two levels (the Tooth level and the Individual level). The Chi-square test will be executed to assess the bivariate association between the outcome and sociodemographic variables. Kaplan–Meier survival analysis will be conducted on the censored data for the survival of the restoration. The difference between survival curves will be assessed by the Mandel—Haenszel log-rank test. Factors affecting survival rates will be assessed using the Cox-proportionality regression method. Between the two groups, the arrest of active carious lesion and survival of the restoration will be compared on the 7th day, 30thday, and at the end of the 6th month of the study visit. If there is a variation in outcome in patients with multiple restorations, tooth level analysis will be carried out.

Subgroup analysis will be performed at the tooth level (type of cavity; class1 and class 2, maxillary and mandibular teeth, premolar and molar)

We intend to have two sets of analyses.

The intention-to-treat analysis (including all randomized patients irrespective of whether they have or have not received the prescribed treatment).The per-protocol analysis.

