## 5. Analysis of Population and Missing Data

The reasons for participant withdrawal would be qualitatively compared for each randomization group and reported. The effect of missing data on the results will be assessed using sensitivity analysis of the augmented data sets. The individual dropouts will be included in the analysis, which would be carried out by multiple imputation methods for missing data.

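### Withdrawing participants for missed appointments, and tying analysis to two completed revisits, prevents month-6 data collection and conflicts with the intention-to-treat and imputation plans

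*Protocol article*

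**What the plan says.** Section 2.13 deals with attendance at review visits. "The appointments may be rescheduled two days earlier or later", at the participant's wish or after a missed appointment. Then: "Non-compliance will be recorded if the participant fails to report for two rescheduled appointments, and the participant will be withdrawn from the trial". An exception follows: "if the subject completes two revisits and thereafter becomes non-compliant, the person-time of participation in the clinical trial will be included in the analysis".

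Four other places bear on this rule.

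- **Section 2.12** states that "an appropriate effort will be taken to follow the study participant for the entire study period of six months".
- **Section 2.8.1** sets three revisits: "The follow-up will be conducted on the 7th and 30th days, and the end of the 6th month to evaluate the survival of the restoration". Section 2.8.2, also under primary outcomes, restricts the radiographic evaluation of arrest to month 6.
- **Section 4** plans an intention-to-treat (ITT) analysis, "including all randomized patients irrespective of whether they have or have not received the prescribed treatment", and a per-protocol analysis that it does not define further.
- **Section 5** says: "The individual dropouts will be included in the analysis, which would be carried out by multiple imputation methods for missing data". It sets no minimum number of visits.

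**The concern.** Both arms are treated in a single baseline procedure (Section 2.7). A missed review visit is therefore only a gap in observation and no departure from treatment. Section 2.13 nevertheless makes it a reason to end follow-up, and then makes use of the person-time depend on how many revisits came first.

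Two things are at stake. First, the trial stops seeking a primary outcome that it might still have obtained. Second, if the two-revisit condition is applied, the analysed set is selected on behaviour after randomisation. Section 2.12 says that neither the participant nor the principal investigator can be blinded. Section 2.14 lists a metallic taste and pigmentation from SDF, which only one arm receives. Early loss of a filling is itself an outcome and could affect whether someone returns. The blinded radiograph readers in Section 2.8.2 do not protect against this, because they can read only the radiographs that are taken.

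**Working it through.** **1. Who is affected.** Section 2.13 does not say whether the two failed rescheduled appointments belong to one visit or to different visits, so both readings are shown. With only three revisits (day 7, day 30, month 6), the exception covers those who attend days 7 and 30 and then miss month 6.

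| Attendance | Section 2.13, same-visit reading | Section 2.13, different-visits reading | Sections 4 and 5 |
|---|---|---|---|
| Fails day 7 only | Withdrawn, no month-6 radiograph, person-time by implication out | Stays in | In ITT; missing data imputed |
| Attends day 7, fails day 30 | Withdrawn, no month-6 radiograph, person-time by implication out | Stays in | In ITT; missing data imputed |
| Fails day 7 and day 30 | Already withdrawn | Withdrawn, no month-6 radiograph, person-time by implication out | In ITT; missing data imputed |
| Attends days 7 and 30, fails month 6 | Person-time in; no radiograph under any rule | Same | In ITT; missing data imputed |

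Under either reading some participants are withdrawn before the only radiographic evaluation, against the six-month follow-up intention in Section 2.12. Under the same-visit reading, the second row also matters for restoration survival. A filling already found to have failed on day 7 would by implication drop out of the analysis if that participant then missed day 30.

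**2. Where the conflict lies.** Withdrawal alone can coexist with Section 5, because a withdrawn participant is a dropout whose outcome can be imputed. The conflict comes from the two-revisit condition. Section 2.13 attaches it to the analysis in general, while Sections 4 and 5 admit everyone.

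**3. The plan's sample size, reproduced.** Inputs from Section 2.11: effect size 0.4, alpha 0.05, power 80%, 100 per group, 10% attrition, 110 per group. Two-sided testing and a standardised mean difference are assumed, as neither is stated. One-sided testing would give 78 per group.

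- Normal approximation: n = 2(1.960 + 0.842)² / 0.4² = 15.70 / 0.16 = 98.1, so 99. The t-test solution is 99.08, so 100, as stated.
- Attrition: 100 × 1.10 = 110, as stated. Dividing by 0.90 gives 112, a difference of no consequence here.

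**4. Power by loss (t-test, d = 0.4, two-sided 0.05).** Only 10% is in the plan; 20% and 30% are assumptions.

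| Loss | Analysed per arm | Power |
|---|---|---|
| 0% | 110 | 84.0% |
| 10% | 110 × 0.90 = 99 | 80.0% |
| 20% | 110 × 0.80 = 88 | 75.1% |
| 30% | 110 × 0.70 = 77 | 69.4% |

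**5. Scale of possible bias (illustration only; every input is assumed).** Take true arrest of 0.80 against 0.65, a difference of 0.15. Suppose failures are twice as likely as successes to be missing, and that only observed outcomes are analysed. With true proportion p and overall loss L, the loss among successes is m = L / (p + 2(1 − p)). The observed proportion is p(1 − m) / [p(1 − m) + (1 − p)(1 − 2m)].

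- L = 20%, p = 0.80: m = 0.20 / 1.20 = 0.167, observed 0.667 / (0.667 + 0.133) = 0.833.
- L = 20%, p = 0.65: m = 0.20 / 1.35 = 0.148, observed 0.554 / (0.554 + 0.246) = 0.692.
- Same pattern in both arms: 0.833 − 0.692 = 0.141, little changed.
- Pattern in one arm only: 0.833 − 0.65 = 0.183, or 0.80 − 0.692 = 0.108.
- At L = 10% the observed proportions are 0.815 and 0.669. The differences are 0.146 (both arms), 0.165 or 0.131 (one arm only).

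Bias of any size thus needs missingness that works differently in the two arms. The protocol gives no figure for that.

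**The case against.** The best defence is that Sections 4 and 5 already commit to all randomised patients, multiple imputation, sensitivity analysis and a comparison of withdrawal reasons by arm. On that view the two-revisit sentence belongs to the per-protocol set, where an attendance condition is reasonable. That is a sensible intention, but Section 2.13 does not state it, so the rule is at best not assigned to an analysis set.

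Several stronger readings are tempting and are not supported.

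- A reader might infer that the month-6 radiograph is the only arrest measurement. It is the only radiographic one; Section 4 and Table 1 also place caries arrest at days 7 and 30.
- A reader might infer that month-6 results are thrown away. They are never collected for those withdrawn earlier.
- A reader might take exclusion below two revisits as written policy. It follows from the sense of the exception, which says only who is included.
- A reader might conclude that one missed visit always costs the primary outcome. That holds only under the same-visit reading.
- A reader might attribute a given loss of power to the rule, or suppose that most of it is avoidable. The protocol gives no rate of missed visits, and people who fail rescheduled appointments despite reminders may not come at month 6 either.

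**Conclusion.** The point holds as a problem of wording and design that should be corrected. Followed literally, Section 2.13 stops the trial from seeking the radiographic primary outcome in participants who may still be willing to provide it, contrary to Section 2.12. Its two-revisit condition cannot be applied to the ITT analysis together with Sections 4 and 5.

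The main harm is missing data that the rule itself creates and possible selection on attendance in an open-label trial. The size of either is unknown. The effect on power is secondary: about 5 percentage points between the planned 10% loss and an assumed 20%, on a t-test reading of the plan's effect size. The sample size is not affected. The conclusion about the analysis set rests on the natural but implied reading of the exception, and on the absence of any words limiting it to the per-protocol set.

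**What to change.** - In Section 2.13, separate a missed visit from withdrawal of consent, and delete withdrawal for missed appointments. This also removes the doubt over whether the two appointments belong to one visit.
- Seek the month-6 examination and radiograph from every randomised participant who has not withdrawn consent, whatever visits were missed before, and record the actual date.
- Delete the two-revisit condition from the ITT analysis. Every randomised participant then contributes observed time to the last examination and a month-6 outcome, observed or imputed, in line with Sections 4 and 5.
- If an attendance condition is still wanted, use it only to define the per-protocol set, and say so in Section 4.

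The cost is a change of wording and a few more calls under the reminder system already planned. Some month-6 visits will be late. The target of 110 per group stays the same.

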### 2.14. Adverse Events

38% SDF solution and glass ionomer cement, employed in regular dental practice for standard dental procedures, are the agents used for this trial. There are minimal potential risks for the study participants, such as the risk for the patients receiving oral care in a routine clinical setting. The most expected adverse effect is an allergic reaction to SDF. All grades of adverse events occurring to the participants during the treatment and follow-up period will be recorded and reported. The principal investigator would obtain information about adverse events with the help of standard questions and an oral examination at every planned visit of the study participant.

The participants may experience an unpleasant metallic taste. Silver diamine fluoride can cause a “transient pigmentation” of the skin, buccal mucosa, or tooth surface. This is not harmful and resolves itself with exfoliation of skin and mucosa within 2 weeks. Universal precautions would be taken to prevent exposures. A cotton roll isolation of the concerned tooth and application of cocoa butter would be carried out to protect surrounding oral tissues from accidental exposure to SDF.

## 3. Close-Out Procedures

The date of the final visit (6 months from the baseline) of the last randomized participant would be the end of the trial date. Regardless of timing and circumstances, the close-out of the trial will proceed in two stages: analysis and documentation of study results, debriefing of participants, and dissemination of study results.

## 4. Statistical Methods

The observed data will be coded, tabulated, and analyzed using Statistical Package for Social Sciences (version 20). We will assess the outcomes at two levels (the Tooth level and the Individual level). The Chi-square test will be executed to assess the bivariate association between the outcome and sociodemographic variables. Kaplan–Meier survival analysis will be conducted on the censored data for the survival of the restoration. The difference between survival curves will be assessed by the Mandel—Haenszel log-rank test. Factors affecting survival rates will be assessed using the Cox-proportionality regression method. Between the two groups, the arrest of active carious lesion and survival of the restoration will be compared on the 7th day, 30thday, and at the end of the 6th month of the study visit. If there is a variation in outcome in patients with multiple restorations, tooth level analysis will be carried out.

Subgroup analysis will be performed at the tooth level (type of cavity; class1 and class 2, maxillary and mandibular teeth, premolar and molar)

We intend to have two sets of analyses.

The intention-to-treat analysis (including all randomized patients irrespective of whether they have or have not received the prescribed treatment).The per-protocol analysis.

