## 2. Methods

### 2.1. Study Design

This is a randomized, controlled trial with two parallel comparator arms, having a 1:1 allocation ratio (Figure 1).

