### 2.7. Interventions

After patient selection, the treatment will be given to the patient according to the selection process. The study participants will be allocated to either one of two parallel arms.

Study arm 1: will receive SDF application and ART restoration.

Study arm 2: will receive ART restoration.

All treatment will be done in a dental chair.

At the baseline visit, an assessment of cavitated caries lesions will be done on all the study participants. The ADA Caries Risk Assessment Form (Age > 6) would be used to assess the risk. Depending on the study arm, ART with or without SDF will be applied to selected teeth (Figure 1). The demographic features of participants and their caries status will be recorded.

*Procedure to be followed for study arm 1:*

A preoperative photograph of the selected tooth will be taken. The caries lesion entrance will be widened and with help of a dental hatchet, the thin unsupported frangible enamel will be removed. In the next step, the decayed tissue will be excavated with a spoon excavator, first at the dentin enamel junction and thereafter from cavity walls and the pulpal floor. The cavity will then be rinsed with water and air-dried, followed by isolation with cotton rolls.

*Application of Silver Diamine Fluoride*

Using a disposable micro applicator tip, the SDF (e-SDF, 38% silver diamine fluoride, Kids-e-dental LLP, Globus Medisys, Mumbai, India) will be applied to the walls of the prepared cavity for 10 s and allowed to air dry for one minute. One drop of 38% SDF solution (2.24 F-ion mg/dose) would be required per tooth. A saturated solution of potassium iodide (Lugol’s Iodine solution 5%, Bio balance, Pali Marwar, Rajasthan, India) will be applied with a different microsponge to decrease color change and will be repeated 1-3 times until no further black discoloration is observed [17].

*Placement of ART restoration*

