### 2.12. Study Implementation

The adult patients visiting for routine dental care to dental school will be recruited for the study. A clinical examination will be carried out on prospective participants. If the individual satisfies the inclusion criteria, the participant will be informed of the options for caries prevention by ART ± SDF. If they agree, they would be offered the choice of participation in the trial and the consenting process will be followed. The patient screening will continue till the target population is attained (n = 220).

Enrolment of the study population will be done over 24 months and follow-up visits are expected to be completed at the end of the 30th month, which will be followed by analysis and report writing. The total study duration is of three years.

The selected participants for the trial will be randomly allocated to a study arm, as per computer-generated randomization. The randomization code will not be revealed to the principal investigator until the participant has been recruited into the clinical trial after all the baseline assessments are complete. This is to ensure allocation concealment. Opaque-sealed envelopes containing randomization codes, in compliance with the randomization list, will be employed for allocation concealment. The randomization will be conducted by the research assistant. The randomization list will remain with the trial coordinator for the whole duration of the research. Due to the apparent nature of the treatment involved, neither the study participant nor the principal investigator (PI) can be blinded.

The PI will be trained for the study requirements, standardized in the assessment of the coronal carious lesion, caries cessation, 38% SDF application and ART, or ART alone, eliciting the required details from the study subjects in a consistent replicable method, and counseling for compliance. The procedure to be conducted and the data to be collected at each study visit will be inspected in detail. During the training sessions, details about procuring and entering the quality data in the clinical record forms will also be discussed. Calibration of PI (AV) will be done before and during the study by another clinical expert (CJ) and reliability will be expressed using Cohen’s kappa statistic.

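### Optional efficiency gain: neither primary outcome has a stated adjusted treatment comparison, although cavity class and caries risk are available at baseline

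*Protocol article*

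**What the plan says.** All analysis statements are in the protocol article, section 4 (Statistical Methods).

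- **Survival of the restoration.** After Kaplan–Meier curves: "The difference between survival curves will be assessed by the Mandel—Haenszel log-rank test". No covariate or stratum is attached to it.
- **Cox model.** The next sentence reads: "Factors affecting survival rates will be assessed using the Cox-proportionality regression method". It lists no covariates and does not say that the model contains the arm or supplies the treatment estimate.
- **Caries arrest.** "Between the two groups, the arrest of active carious lesion and survival of the restoration will be compared on the 7th day" and at the two later visits; no test or model is named.
- **Chi-square test.** This has another task: "The Chi-square test will be executed to assess the bivariate association between the outcome and sociodemographic variables".
- **Baseline factors.** Tooth-level subgroups are "type of cavity; class1 and class 2, maxillary and mandibular teeth, premolar and molar", so these factors must be recorded. Section 2.7 adds: "The ADA Caries Risk Assessment Form (Age > 6) would be used to assess the risk". The risk form does not reappear in section 4.
- **Allocation.** Section 2.1 describes a design "having a 1:1 allocation ratio". Section 2.12 says participants are "randomly allocated to a study arm, as per computer-generated randomization"; it names no stratification factor.

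**The concern.** The plan regards cavity class as important enough for a subgroup analysis and collects a caries-risk assessment on every participant. As written, it uses the first only to split the data and gives the second no analysis role. If these factors predict arrest or restoration failure, a comparison that ignores them is less precise than it could be, and a chance imbalance between the arms stays in the point estimate. With a sample size set for 80% power there is little slack. An unlisted set of Cox factors also leaves open which covariates enter and when they are chosen.

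**Working it through.** **1. The plan's own figure.** Section 2.11 gives effect size 0.4, alpha 0.05, 80% power and 100 per group. Read as a two-sided standardised mean difference: n = 2 × (1.96 + 0.842)² / 0.4² = 98.1, so 99 per group; the t-test version gives 99.08, so 100. With 10% attrition, 99 / 0.9 = 110. The stated figures reproduce, with no allowance for covariates. The checks below use 99 or 100 per arm.

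**2. Size of a chance imbalance.** Assume half of the lesions are Class 2 (not in the documents).
- 95% limit of the imbalance: 1.96 × √(2 × 0.25 / 99) = 0.139, about 14 points.
- If Class 2 does 10 to 20 points worse (assumption), the arm difference shifts by 0.139 × 0.10 to 0.139 × 0.20, or 1.4 to 2.8 points. At one standard deviation of imbalance (7 points) the shift is 0.7 to 1.4 points.
- For scale, at an assumed 80% success the standard error of the arm difference is √(2 × 0.16 / 99) = 0.057, or 5.7 points. Even the extreme shift is about half a standard error (2.8 / 5.7 = 0.49), and that standard error already allows for it.

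**3. Month-6 arrest, by simulation.** 198 patients, one lesion each, analysed as a raw risk difference or as a standardised difference from a logistic model with arm, cavity class and a three-level risk score. Class log-odds were 0.7, 1.1 and 1.5, with risk log-odds 0.3, 0.5 and 0.8 per level. All of these strengths are assumptions, as is the three-level scoring.

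| Assumed prognosis | Variance reduction at 60–75% arrest |
|---|---|
| Weak | about 1–3% |
| Moderate | about 5–8% |
| Strong | about 8–16% |

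Type I error stayed near 5%. At 90% arrest the gain is little unless prognosis is strong.

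**4. Survival, by simulation.** 100 per arm, exponential failure times censored at six months, one 50% binary covariate, 600 runs (simulation error about 2 points). The two scenarios are 20% failure with treatment hazard ratio 0.4, and 30% with 0.5.

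| Covariate hazard ratio | Log-rank power | Adjusted Cox power |
|---|---|---|
| 1 | 66%, 64% | 65%, 63% |
| 2 | 68%, 67% | 67%, 68% |
| 4 | 72%, 66% | 73%, 70% |

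The gain is about 0 to 5 points and shows only with a very strong covariate. With no treatment effect, the log-rank test rejected in 4.8 to 6.2% of runs and adjusted Cox in 4.2 to 6.3%, both 5% within simulation error.

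**5. How many covariates survival can carry.** The Introduction cites ART success of 79% at one year and survival of 84% at two years. At constant hazard (assumption), failure by six months is 1 − 0.79^(1/2) = 11.1% or 1 − 0.84^(1/4) = 4.3%. With 198 single restorations that is 198 × 0.043 to 198 × 0.111, roughly 8 to 22 failures.
- Arm, class, tooth type, jaw and a three-level risk score take 6 parameters: 8/6 to 22/6, about 1 to 4 failures each.
- Arm, class and three-level risk take 4: 8/4 to 22/4, about 2 to 5.5 each. Even the short list is tight.

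**The case against.** The strongest case against is that nothing here is wrong. An unadjusted log-rank test in a 1:1 randomised trial keeps its type I error, a regression is already planned in the next sentence, and a condensed article may leave its covariate list to an analysis plan that is not shown. The gain depends on prognostic strengths the documents do not give, and is small in the weak case. Adjustment also has a price: the survival model could be overloaded, and cavity class has no single value for a person with several lesions.

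Most of this stands. It removes any claim of error and rules out a long covariate list. What remains is that the article fixes an unadjusted test as the survival comparison and gives the Cox model a different purpose, so the better use of data already collected is not stated.

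A reader might infer more than the text supports:
- *That the results would be biased.* Chance imbalance under randomisation is not bias; the test and its standard error already allow for it.
- *That both outcomes are compared by unadjusted tests.* For arrest no test is named, and silence is not an unadjusted test.
- *That randomisation is unstratified.* The article names no factor, which does not show that there is none.
- *That the Cox model excludes the arm.* Its contents are simply not stated.

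**Conclusion.** The point holds as an optional efficiency and prespecification improvement. The article states no adjusted treatment comparison for either primary outcome, while cavity class and ADA caries risk are available for one. The expected gain is about 1 to 16% lower variance for arrest at arrest rates of 60 to 75%, less at 90%, and about 0 to 5 points of power for survival. These ranges rest on assumed prognostic strengths, a half-and-half split of cavity class in the imbalance figure, and one lesion per person. The case is stronger for arrest than for survival, where few failures are likely and the measurable gain needs a very strong covariate.

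**What to change.** - **Arrest at month 6.** Prespecify the main arm comparison as a regression with arm, cavity class and ADA caries risk, reported as a standardised risk difference with person-level robust standard errors. State how the risk form is scored.
- **Survival.** State that the Cox model contains arm plus the same short list, or stratify the log-rank test by cavity class, which is the safer choice if failures are near the low end of 8 to 22. Keep the unadjusted log-rank test as supportive.
- **Jaw and premolar/molar.** Add these only if the number of events allows, under a rule set in advance.
- **Individual-level analysis.** Say how a tooth-level covariate is defined for a person with several lesions, for example any Class 2 lesion present.

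The cost is analysis wording, with no new data or visits. The covariates and their coding must be fixed before outcomes are seen by arm, and the survival model must be kept small.
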